### Implementation outcomes

We will use the RE-AIM theoretical framework^27^ to evaluate implementation outcomes, as delineated in table 1.

**Table 1 T1:** Implementation outcomes following the RE-AIM framework

	R Reach	E Effectiveness	A Adoption	I Implementation fidelity	M Maintenance
Type I effectiveness-implementation hybrid RCT	Proportion reached Representativity	Knowledge Attitudes Skills Behaviours	Proportion completing the I-CARE programme Satisfaction with the training programme	Technical incidents Time spent on the different learning activities Use of supplementary materials	Intention to continue to train on LGBTI health and healthcare Outcomes at the 3-month follow-up

I-CARE, Improving Care and Access for Rainbow Equity; LGBTI, lesbian, gay, bisexual, transgender or non-binary and intersex; RCT, randomised controlled trial.

The reach dimension will be assessed by comparing the number and sociodemographic characteristics of participants with those of the source population. Adoption will be evaluated based on the proportion of participants allocated to the I-CARE group who complete the training programme, along with postintervention items assessing participants’ satisfaction with the I-CARE content, format, ease of use and relevance to clinical practice.

### Data collection instruments

The primary outcomes, knowledge and attitudes, will be assessed using two subscales of the *QUeering Individual Relational and Knowledge Scales* for providers (QUIRKS-Provider).^28^ Reliability estimates based on McDonald’s omega support the unidimensionality of each subscale (knowledge: ω=0.75; attitudes: ω=0.69). Validity evidence indicates strong and statistically significant correlations between these subscales and the corresponding domains of *the Lesbian, Gay, Bisexual, and Transgender Development of Clinical Skills Scale* (LGBT-DOCSS), another validated instrument.^29^

Secondary outcomes will be assessed as follows. *Skills* will be measured using the *Clinical Preparedness* subscale of the LGBT-DOCSS. *Self-reported behaviours* will be assessed using 11 of the 15 items from the *Behaviour* subscale of the *Gay Affirmative Practice Scale* (GAP).^30^ Consistent with prior research,^31^ the wording of the GAP items was adapted to enhance inclusivity and contextual relevance (eg, replacing ‘gay/lesbian’ with ‘LGBTI’ and ‘clients’ with ‘patients’). Participants will also report on the presence of LGBTI-friendly environmental cues in their practice setting using the corresponding QUIRKS-Provider subscale (4 items).

The scales were translated and culturally adapted from English into French following the *International Society for Pharmacoeconomics and Outcomes Research* (ISPOR) guidelines,^32^ including two independent forward translations (one by a team member and one by a professional translator), followed by back-translation, comparison and harmonisation of the versions. Cognitive debriefing was conducted as a final step. All translations and modifications of the standardised scales and subscales were carried out in agreement with the original authors. The full translation report, including details of the modifications, is available on request.

### Sample size calculations

Based on previous research,^33^ we expect an effect size of Cohen’s d=0.31 on the Knowledge subscale of the QUIRKS-Provider scale. Using generalised estimating equations (GEE),^34^ and assuming 80% power, a two-sided significance level of 0.05, an intraindividual correlation of 0.4, and 20% loss to follow-up, we estimated that 474 participants would be required to detect this effect at the postintervention assessment. Recruiting this number of participants appears feasible, even with a low participation rate. As the marginal cost of including additional participants is negligible, no upper limit on the sample size has been set.

### Statistical analyses

We will first compare the two study groups with respect to sociodemographic characteristics and baseline measures of interest (knowledge, attitudes, skills, behaviours and environmental cues) to assess the extent of any baseline imbalance. We will then assess the representativeness of the study sample relative to the source population using data from Swiss medical registries.

Differences in the effectiveness outcomes over time and between study arms will be analysed using GEE.^35
36^ The model will include indicators for follow-up time points, study arm and their interaction, allowing estimation of differential changes in outcomes between groups at each time point. When appropriate, analyses will adjust for key baseline characteristics (eg, participating physicians’ sexual orientation and gender identity, which may be associated with baseline competence in LGBTI health) to improve precision and mitigate potential imbalance. The model is specified as follows:

(1)
$$\mu_{it}=\beta_{0}+\beta_{T1}T1_{it}+\beta_{T2}T2_{it}+\beta_{IT1}(I_{i}\times T1_{it})+\beta_{IT2}(I_{i}\times T2_{it})+\gamma X_{i}$$

where

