## Methods and analysis

### Study design and setting

This study is a type I effectiveness–implementation hybrid, two-arm, parallel-group, superiority randomised controlled trial with a 1:1 allocation ratio. It is conducted among PCPs practising in the French-speaking cantons of Switzerland (Fribourg, Geneva, Jura, Neuchâtel, Valais, Vaud and Bern), which comprise about one quarter of the Swiss population. Participants are individually randomised to receive either the I-CARE e-learning programme (intervention) or an active control e-learning programme on MI, matched for format and duration. Outcomes are assessed at baseline, immediately postintervention, and at the 3-month follow-up assessment. Participants are partially blinded to the specific study hypothesis but not to group allocation. The trial incorporates implementation outcomes evaluated using the RE-AIM framework.

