### Randomisation

Each participant who completes the baseline questionnaire will be randomised (1:1) to either the intervention group, receiving an invitation and access to the I-CARE e-learning programme, or the control group. The randomisation will be stratified by sex assigned at birth (male or female) and age category, as physicians’ attitudes towards sexual and gender minorities have been shown to vary by gender and by generation, with earlier year of graduation and male gender predicting more stigmatising responses.^24
25^ Stratification protects against chance imbalance between arms on these prognostic factors. Three age categories will be used: PCPs born after 1980 (Generation Z and Millennials); PCPs born between 1965 and 1980 (Generation X) and PCPs born before 1965 (Baby Boomers generation or older ones if any). Allocation tables will be generated using Stata V.19 (StataCorp LLC, College Station, Texas) with block randomisation (block size of four) to ensure balanced distribution between the intervention and control groups.^26^ Participant allocation will be implemented automatically in REDCap.

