### Ethics and dissemination

The study does not entail any specific risks or side effects for participants. Participation is voluntary, and participants may withdraw at any time without providing a reason and without any consequences. This right will be clearly stated in the information sheet prior to enrolment. All data will be coded. The correspondence between coded identifiers and email addresses will be known only to the Unisanté IT specialists responsible for the technical management of the REDCap interface, the principal investigator and the project’s postdoctoral researcher. Participants will also be informed that they may decline to answer sensitive questions. In the unlikely event of harm related to trial participation, appropriate measures will be taken in accordance with applicable Swiss legal and institutional requirements. The project was approved by the Central Ethics Commission of the University of Lausanne (CER-UNIL) on 7 July 2025.

A three-part communication strategy will be implemented to disseminate the objectives, findings and potential implementation of the I-CARE e-learning programme. The first component will target the public and will include a press conference, coverage in Swiss mainstream media and communication via social media. It will present the study findings and highlight the impact of the I-CARE programme on PCPs’ knowledge, attitudes, skills and behaviours in caring for LGBTI patients, with the aim of raising awareness of LGBTI health equity and reducing stigma.

The second component will target PCPs and the scientific community and will involve publication of scientific articles, presentations at medical conferences, podcasts and dissemination of newsletters through medical societies. We will also collaborate with the Swiss Health Network for Equity (https://www.health-equity-network.ch/en/), which has expressed its interest in disseminating the study findings through its network. Communication efforts will be tailored to motivate PCPs who have not yet participated in the I-CARE e-learning programme.

The third component will target LGBTI communities and will rely on cantonal and national LGBTI organisations to disseminate the study findings among LGBTI individuals in Switzerland. These communities will also be informed about the availability of a list of PCPs who have completed the I-CARE programme and consented to being publicly identified as such.

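### The primary model is not tied to the randomisation strata (sex and age category): a small loss of reported precision without bias, and free to remove

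*Protocol article*

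**What the plan says.** The Randomisation section of the protocol article states: "The randomisation will be stratified by sex assigned at birth (male or female) and age category". There are three birth cohorts, hence six strata, filled in blocks of four. The reason given is that male gender and earlier graduation predict more stigmatising responses, and the section adds: "Stratification protects against chance imbalance between arms on these prognostic factors".

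The Statistical analyses section sets out a GEE with a common baseline mean for the two arms and a covariate vector X_i, which is defined only as the adjustment covariates. On what goes into it, the text says: "When appropriate, analyses will adjust for key baseline characteristics". The examples are the physician's sexual orientation and gender identity. The stated aims are to gain precision and to offset possible imbalance. Sex and age come back only as effect modifiers, under Additional research objectives.

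Under Ethics and dissemination: "Participants will also be informed that they may decline to answer sensitive questions". Which questions count as sensitive is not stated. The Study procedure section makes unnamed key fields mandatory, and the Statistical analyses section allows multiple imputation depending on how much is missing.

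**The concern.** Stratified blocks make the arms more alike on sex and age than simple randomisation would. If those factors predict the outcome, the true sampling variance of the between-arm difference falls. A model without the strata still estimates the variance as if allocation had been unstratified, and so does a robust variance that treats participants as independent. The confidence intervals are then a little wider than the design has earned. The estimate itself is unaffected.

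The protocol therefore builds two factors into the design on prognostic grounds, and its analysis rule does not carry them over. The wording also leaves open whether the primary model is adjusted at all, and for what.

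A second, conditional matter concerns the examples. If sexual orientation or gender identity enters X_i and some physicians decline to answer, software that defaults to complete cases would leave them out of the adjusted model.

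**Working it through.** **Inputs from the protocol.** The Sample size calculations section expects "d=0.31 on the Knowledge subscale of the QUIRKS-Provider scale", "assuming 80% power, a two-sided significance level of 0.05, an intraindividual correlation of 0.4, and 20% loss to follow-up", and concludes: "we estimated that 474 participants would be required to detect this effect at the postintervention assessment". The Study design section gives a "superiority randomised controlled trial with a 1:1 allocation ratio".

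**Assumed inputs.** The protocol gives no figure for R², the share of outcome variance explained by the strata. I take 5–10%, with 2% as a low case.

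**1. The plan's own figure.** One route returns it exactly. With change-score variance 2(1 − 0.4) = 1.2, n per arm = 2 × 1.2 × ((1.960 + 0.842)/0.31)² = 196.02, rounded up to 197. Then 197 × 1.2 = 236.4, rounded up to 237, and 2 × 237 = 474. So d = 0.31 and ρ = 0.4 are usable as read.

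**2. Variance with and without the strata.** In the constrained model with exchangeable correlation, the variance factor without strata is 1 − ρ² = 1 − 0.16 = 0.84. With strata explaining R² at each visit, the residual correlation is ρ' = (0.4 − R²)/(1 − R²) and the factor is V = (1 − R²)(1 − ρ'²).

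- R² = 5%: ρ' = 0.35/0.95 = 0.368; V = 0.95 × 0.8643 = 0.8211; ratio 0.8211/0.84 = 0.977.
- R² = 10%: ρ' = 0.30/0.90 = 0.333; V = 0.90 × 0.8889 = 0.8000; ratio 0.8000/0.84 = 0.952.

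**3. Power and actual alpha.** With 474 × 0.8 = 379 analysed, there are 189.6 per arm.

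- With strata: power = Φ(0.31/√(2V/189.6) − 1.96).
- Without strata: the true variance is still V, but the test uses 0.84, so power = Φ(0.31/√(2V/189.6) − 1.96√(0.84/V)).
- Actual alpha without strata = 2(1 − Φ(1.96√(0.84/V))).

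| Assumed R² | Variance cut | SE cut | Power without → with | Actual alpha without |
|---|---|---|---|---|
| 2% | 0.9% | 0.4% | 91.0% → 91.1% | 0.049 |
| 5% | 2.3% | 1.1% | 91.1% → 91.5% | 0.047 |
| 10% | 4.8% | 2.4% | 91.4% → 92.1% | 0.045 |

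**4. Working independence instead of exchangeable.** The factors become 1 and 1 − R². At R² = 5% and 10%, power goes from 86.1% to 87.2% and from 86.8% to 88.9%. Actual alpha without strata is 0.044 and 0.039.

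**5. Simulation check.** I used 4,000 trials per setting, 380 participants, six strata, blocks of four, and ANCOVA as a stand-in for the complete-data constrained model. At R² = 2%, 5% and 10%:

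- The ratio of SE with strata to SE without is 0.996, 0.989 and 0.976.
- Power goes from 91.1% to 91.1%, 91.3% to 91.4%, and 91.5% to 92.4%.
- The false-positive rate without strata is 0.0508, 0.0448 and 0.0415, with Monte Carlo error √(0.05 × 0.95/4000) ≈ 0.003.

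This agrees with step 3.

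**6. Declined covariates (illustration only).** The protocol gives no decline rate. If 5% or 10% declined and were dropped, 474 × 0.05 ≈ 24 or 474 × 0.10 ≈ 47 randomised physicians would leave the adjusted model. Constrained-model power (variance 0.84) would go from 90.9% to 89.4% or 87.8%, before counting any precision the covariate adds.

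**The case against.** The best defence is that this is a journal article. Its covariates are introduced as examples, nothing excludes sex and age from X_i, and the full list may stand in an analysis plan that is not shown. Moreover, the stated purpose of stratifying is protection against chance imbalance, and stratified blocks deliver that whatever the model contains. This stands as far as a missing list goes: a missing list is no finding. It does not answer the point about the rule that is printed, which makes adjustment conditional and names neither stratification factor.

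The defence is also right that the gain is small. The model already uses the baseline outcome, which absorbs part of what sex and age explain, and the error is on the conservative side.

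Two stronger readings are tempting, and the documents support neither:

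- **Covariates chosen from observed imbalance.** A reader might infer this because a baseline comparison comes first and imbalance is one stated aim of adjustment. But the text states no selection rule, names precision first, and speaks of imbalance as a possibility. The wording is open; it is not a data-driven trigger.
- **Physicians will be dropped from the primary analysis.** The protocol does not say which items may be declined, makes some unnamed fields mandatory, foresees imputation, and nowhere states complete-case handling. It is also a separate matter from the strata: with no adjustment, nobody is lost for a missing covariate.

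**Conclusion.** The point holds as a small mismatch between design and analysis. Randomisation is stratified on factors the protocol calls prognostic, and the primary GEE as described may be run without them. In that case the reported standard errors are about 1.1–2.4% too large in the constrained model, the two-sided test runs at about 0.047–0.045 instead of 0.05, and less than one point of power is lost. Under working independence the loss is about one to two points. There is no bias and no excess of false positives.

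These sizes rest on an assumed R² of 5–10% and the protocol's ρ of 0.4. The protocol ties the strata to attitudes only. For knowledge, the outcome that sized the trial, a prognostic role is my assumption, and the gain could be close to nil. The exclusion of decliners is a conditional risk of unknown size, and the figures in step 6 of the working should not be read as an estimate.

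**What to change.** State in the Statistical analyses section that sex assigned at birth and the three age categories always enter X_i in the primary effectiveness models. Replace the conditional wording with a commitment to fix any further covariates before outcome data are compared between arms.

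If sexual orientation or gender identity is kept as a covariate and may be declined, add how decliners stay in the model: for example, a separate category for non-disclosure, or the imputation the protocol already foresees. Either would do.

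The cost is a sentence or two. Both stratification variables will be complete, because allocation cannot proceed without them, and at most five extra parameters (six strata) are needed with 474 participants. Recruitment began in July 2026 and data collection runs into 2028, so there is time to settle this before any comparison of outcomes.

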**Table IT3:** 

$$\mu_{it}$$	is the expected value of the outcome measure for participant *i* at time *t*, where *t* corresponds to preintervention (*t* = 0), postintervention (*t* = 1) or the 3-month follow-up (*t* = 2);
$$T1_{it}\;\text{and}\;T2_{it}$$	are binary indicators for *t* = 1 and *t* = 2, respectively;
$$I_{i}$$	is a binary indicator of group assignment (0 = control, 1 = intervention);
$$X_{i}$$	represents adjustment covariates;
$$\beta_{0}$$	represents the baseline mean of the outcome measure under the model constraint of equal baseline means across groups;
$$\beta_{T1}\;\text{and}\;\beta_{T2}$$	represent the mean change in the control group from *t* = 0 to *t* = 1 and from *t* = 0 to *t* = 2, respectively;
$$\beta_{IT1}\;\text{and}\;\beta_{IT2}$$	represent the between-group differences in change from *t* = 0 to *t* = 1 and from *t* = 0 to *t* = 2, respectively;
γ	represents the regression coefficients associated with the covariates.

In this model, $\beta_{IT1}$ and $\beta_{IT2}$ estimate the intervention effect at the postintervention and 3-month follow-up assessments, respectively. In the presence of substantially different variability in the outcome at different time points, separate models for *t*=1 and *t*=2 may also be considered.

The model does not include separate baseline mean parameters for the two groups. This constraint is justified by randomisation, which implies equal expected baseline means across groups. Moreover, the corresponding unconstrained model has been shown to yield less efficient estimators of the intervention effect.^37^

GEE is a quasi-likelihood approach that provides consistent estimates of regression coefficients and valid inference in the presence of correlated observations, as occurs with repeated measurements within individuals over time. Unlike mixed models (MM), GEE allows direct specification of the working correlation structure and yields valid inference even if this structure is misspecified.^38^

A longitudinal data analysis (LDA) approach, such as GEE or MM, is preferable to an analysis of covariance (ANCOVA) framework, which treats the baseline value as a fixed covariate when modelling postintervention outcomes. One limitation of ANCOVA is that participants with missing baseline or postintervention outcome data are excluded from the analysis, which may reduce statistical power. By contrast, LDA methods use all available repeated measurements. ANCOVA may also underestimate the variance of adjusted group mean estimates because it does not fully account for variability in baseline values.^37
39^ However, there are warnings in the literature against the use of GEE with small sample sizes,^40^ whereas ANCOVA has been shown to have good performance even in small sample scenarios.^41^ ANCOVA might, therefore, be used in case the target sample size is not reached.

To assess the robustness of the findings, sensitivity analyses using MM or ordinary least squares with clustered standard error will be implemented.

Extent and patterns of missing data will be explored. Depending on the proportion of missing data, multiple imputation by chained equations may be implemented.

To address potential attrition, we will compare baseline characteristics of PCPs who complete all follow-up assessments with those of PCPs with missing follow-up data, separately within each study arm. In the presence of substantial differences, modified GEE approaches incorporating inverse probability weighting or multiple imputation will be considered.^42^

In addition to intention-to-treat estimates, we will estimate the complier average causal effect of the I-CARE programme using instrumental variable (IV) methods, where adherence is defined as completion of the full I-CARE programme. Randomised assignment to the I-CARE programme will be used as an IV for completion of the full I-CARE programme, with completion treated as the endogenous regressor and competency outcomes as the dependent variables. Under the standard IV assumptions, including that randomised assignment affects outcomes only through programme completion, IV estimates identify the causal effect of the I-CARE programme among compliers.

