**Figure 1 F1:**
[figure not shown]
Study flow diagram. I-CARE, Improving Care and Access for Rainbow Equity; MI, motivational interviewing; PCPs, primary care physicians.

Once participants have completed their allocated e-learning programme—or, at the latest, 6 weeks after completing the baseline questionnaire if they do not complete the training programme—they will be invited to complete a self-administered online postintervention questionnaire. A final self-administered online follow-up questionnaire will be completed at the 3-month follow-up assessment. Participants who complete all questionnaires and the allocated e-learning programme will receive six CME credits as well as CHF 50 (about USD 64) in compensation. All questionnaires will be hosted online using REDCap (REDCap Consortium, Vanderbilt University, Nashville, Tennessee).^18
19^

All three questionnaires will assess effectiveness outcomes. The baseline questionnaire will also collect sociodemographic characteristics, while the postintervention questionnaire will assess participants’ satisfaction with the training programme. All appropriate measures have been taken to minimise participant errors during questionnaire completion, including prior cognitive testing and pilot testing, explicit drop-down response options, built-in skip logic, mandatory fields for key variables, standardised response formats and range and plausibility checks for numerical entries.

Recruitment began with the pilot phase on 10 July 2026 and is planned to continue until 31 December 2027. Data collection is expected to be completed in 2028, and the study is expected to be completed by 31 March 2029, including publication and dissemination activities.

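### The attrition rules for the primary analysis do not use programme completion, so the available-data GEE may overstate the intention-to-treat effect

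*Protocol article*

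**What the plan says.** The Statistical analyses section of the protocol article makes a GEE with equal baseline means (equation 1) the main analysis, and prefers longitudinal methods to ANCOVA partly because of how they treat incomplete data: "By contrast, LDA methods use all available repeated measurements". Missing data are then covered by two separate statements.

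- Proportion missing: "Extent and patterns of missing data will be explored", followed by "Depending on the proportion of missing data, multiple imputation by chained equations may be implemented".
- Dropout: "we will compare baseline characteristics of PCPs who complete all follow-up assessments with those of PCPs with missing follow-up data, separately within each study arm", followed by "In the presence of substantial differences, modified GEE approaches incorporating inverse probability weighting or multiple imputation will be considered".

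Neither statement gives a threshold, and neither names programme completion. For robustness, "sensitivity analyses using MM or ordinary least squares with clustered standard error will be implemented".

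Three other places bear on this. Study procedure sets the incentive: "Participants who complete all questionnaires and the allocated e-learning programme will receive six CME credits as well as CHF 50". The same section still invites physicians who do not finish the programme to the postintervention questionnaire, at six weeks. Risk of bias names non-random attrition as a concern, but expects little difference between arms because the control programme is also free and carries similar credits.

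**The concern.** The attrition check looks only at variables fixed before randomisation. The incentive points to one that arises afterwards. A physician who abandons the course has forfeited the credits and the CHF 50, and gains nothing further by answering. Non-completers may therefore be over-represented among those missing at the postintervention assessment.

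If they also benefit less from I-CARE, the respondents in that arm are weighted towards completers, and the estimate moves from the intention-to-treat effect towards the effect in completers. This does not need differential attrition. Completion and response can be identical in the two arms, because only the I-CARE arm has an effect that varies with completion. The reassurance in Risk of bias, which concerns differences between arms, therefore does not reach this mechanism.

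The size of the primary effect estimate is at stake. The MM and OLS sensitivity analyses would not reveal the problem, since neither is described as using completion.

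**Working it through.** **Inputs from the protocol** (Sample size calculations): d = 0.31 on Knowledge, two-sided 5% level, 80% power, intraindividual correlation 0.4, 20% loss, N = 474.

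**The plan's own figure.** With the change-score variance factor 2(1 − 0.4) = 1.2, n per arm = 2 × (1.960 + 0.842)² × 1.2 / 0.31² = 2 × 7.85 × 1.2 / 0.0961 = 196.02, rounded up to 197. Then 197 × 1.20 = 236.4, rounded up to 237 per arm, or 474 in total. The article does not print its formula, but this route reproduces the number. It confirms the inputs and fixes the simulated trial size at 237 per arm.

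**Assumed inputs.** The documents give no completion rate, no response rate by completion, and no effect in non-completers. Let p be the proportion completing I-CARE, r_c and r_n the response rates in completers and non-completers, and d_c and d_n their effects.

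- Overall response: p·r_c + (1 − p)·r_n = 0.80
- True intention-to-treat effect: p·d_c + (1 − p)·d_n = 0.31
- Effect among respondents: [p·r_c·d_c + (1 − p)·r_n·d_n] / 0.80

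**Illustration, no gain in non-completers** (p = 0.70, r_c = 0.95, r_n = 0.45):

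- Response: 0.665 + 0.135 = 0.80
- d_c = 0.31/0.70 = 0.443
- Completers among respondents: 0.665/0.80 = 83%
- Effect among respondents: 0.831 × 0.443 = 0.368, which is 19% above 0.31

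**Illustration, non-completers gain half as much:** d_c = 0.31/0.85 = 0.365 and d_n = 0.182. The effect among respondents is 0.831 × 0.365 + 0.169 × 0.182 = 0.334, which is 8% above.

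**Range at 20% loss.** With d_n = 0 the formula reduces to 0.31 × r_c/0.80, so only the completers' response rate matters. The half-gain column covers completion from 60% to 90% where feasible.

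| Completers' response | No gain in non-completers | Half gain |
|---|---|---|
| 85% | 0.329 (+6%) | 0.317 to 0.319 |
| 90% | 0.349 (+13%) | 0.325 to 0.327 |
| 95% | 0.368 (+19%) | 0.332 to 0.336 |
| 100% | 0.387 (+25%) | 0.339 to 0.344 |

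The half-gain column runs from +2% to +11%.

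**Simulation of the equal-baseline GEE** (N = 474, correlation 0.4, 1500 runs). Unless stated, p = 0.70 and response is 95%/45% in both arms.

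| Scenario | True effect | GEE mean | Weighted by arm and completion |
|---|---|---|---|
| Non-completers gain nothing | 0.31 | 0.370 | 0.311 |
| Non-completers gain half | 0.31 | 0.331 | 0.307 |
| Non-completers gain equally | 0.31 | 0.307 | 0.307 |
| Non-completers gain nothing but respond equally (80%) | 0.31 | 0.310 | 0.310 |
| Stronger selection in the control arm | 0.31 | 0.296 | 0.309 |
| No effect, same selection in both arms | 0 | −0.002 | −0.002 |
| No effect, selection in I-CARE only | 0 | 0.049 | 0.004 |

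In the last two rows non-completers score 0.3 SD lower at follow-up, and the rejection rates are 5.1% and 8.5%. The last row uses 80% completion, with 95%/20% response in I-CARE and 80% throughout in control. The control-selection row also has non-completers 0.3 SD lower, with response of 85%/68% in I-CARE and 98%/38% in control.

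**The planned check.** A 5%-level comparison of baseline scores between responders and non-responders in the I-CARE arm is significant in 4% to 7% of runs across these scenarios, which is chance level. Completion was simulated as unrelated to baseline score.

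**Cost in precision.** In a separate simulation of the first scenario, the SD of the estimate was 0.096 on available data and 0.103 after imputation by arm with completion: 0.103/0.096 = 1.07.

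**The case against.** Several stronger readings are tempting, and the article does not support them.

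- **That baseline differences are the only trigger.** They are not. Imputation may also follow from the proportion missing. That rule is discretionary, however, and does not bring completion into the imputation model, without which imputation would not remove this bias.
- **That such dropout would pass undetected.** This goes too far. Missing-data patterns will be explored, with no restriction to baseline variables, and completion is recorded for adoption and for the complier analysis. The chance-level flag rate also follows from simulating completion as independent of baseline; if the two were related, the planned comparison could pick it up. What is absent is any stated link from completion to the primary analysis.
- **That the effect is overstated.** This depends on rates the documents do not give. The 95%/45% contrast is strong, non-completers are invited at six weeks, and the bias can be nil or slightly reversed. In the main illustration the shift is about 0.6 of a standard error (0.057/0.096). Zero gain in non-completers is not arbitrary, since the protocol's own instrumental-variable analysis assumes that assignment acts only through completion. Partial viewing could still confer some benefit, hence the half-gain case.
- **That the protocol makes a false claim for GEE.** The statement that GEE "yields valid inference even if this structure is misspecified" concerns the working correlation and is correct there. It is not a claim about missing data.
- **That false positives are inflated.** With no effect and the same selection in both arms, rejection stays at 5.1%. It rose to 8.5% only with selection confined to I-CARE, an asymmetry that the matched control is meant to limit.

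It is also fair to say that imputation details and thresholds may sit in an analysis plan that is not shown. Their absence is not the point here. The article states what will decide the attrition correction, and that rule looks at variables that need not carry the mechanism its own incentive creates.

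**Conclusion.** The point stands in a conditional form. The stated rules for correcting attrition rest on baseline differences and on the proportion missing, and neither brings in programme completion. The available-data GEE may therefore overstate the intention-to-treat effect on the two primary outcomes if I-CARE non-completers both answer less often and benefit less. Both conditions are needed. The percentages were worked out for Knowledge, the only outcome with a stated effect size, and they rest on assumed completion and response rates. The main harm is to the size of the estimate rather than to the type I error. The change is worth making because the relevant variable is already collected.

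**What to change.** 1. State that missingness at each follow-up will be compared by programme completion within arm, alongside the baseline comparison.
2. For both primary outcomes, run the equation (1) GEE after multiple imputation done separately by arm, with baseline score, the randomisation strata and programme completion or exposure in the imputation model. Inverse probability weights built on the same variables are an alternative. Do not make this conditional on baseline differences or on the proportion missing.
3. Add a missing-not-at-random sensitivity analysis for the two primary outcomes. Recovery of 0.31 in the simulation relies on missingness being at random given completion, which the trial data cannot confirm.

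The cost is revised wording, modest programming and a standard error about 7% larger. No new data are needed: completion must be known in both arms to award the credits, and time spent on the learning activities is already a planned implementation measure.
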